## Background

In high-income countries, strokes are the third leading cause of death after cardiovascular diseases and cancers. In Switzerland, about 16,000 people suffer a stroke each year [1]. However, over the last few decades, the death rate following strokes has continuously declined in developed countries because of improvements in primary care. The corollary to this trend is an increased burden on rehabilitation units because of stroke survivors with severe disabilities [2]. The major long-term disability that hinders stroke survivors in recovering a normal life is partial paralysis affecting the extremities. Six months after a stroke, 50 % of stroke survivors still suffer some degree of hemiparesis and 30 % are unable to walk without assistance [3].

In addition to strokes, other circumstances that damage neural tissue can induce similar disabilities. Traumatic brain injuries (TBI), most commonly induced by falls or road traffic accidents, are also a significant issue in Switzerland, with about 850 severe cases per year [4]. Patients with traumatic spinal cord injuries (SCI), representing about 150 cases per year, can be added to this number [5]. Roughly 50 % of these patients suffer from incomplete injuries and thus exhibit residual locomotor capacities [6].

During the months following an injury to the central nervous system, patients partially recover motor and sensory patterns that were in place before the injury. In stroke patients, the maximum degree of recovery typically occurs within the first 3 months, then it progresses at a slower rate until 6 months have passed [7]. This recovery process is in part driven by brain plasticity. In short, redundant connectivity exists in the brain, and new functional circuits can form via remapping between cortical regions [8, 9]. It has been shown that providing an enriched environment stimulates plasticity and facilitates recovery [9]. Although further studies are needed to better understand brain plasticity in humans [10], neurorehabilitation is largely based on the premise that a set of well-chosen exercises can stimulate neural plasticity and enhance the recovery process.

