### Participants

Study participants will be recruited from among the inpatients admitted for neurorehabilitation at the CRR. Selection of the inclusion criteria was guided by the rationale of reflecting the prevailing choice in neurorehabilitation clinics of specific therapies that are tailored to patients’ needs. A summary of the inclusion/exclusion criteria is shown in Table 2. Potential candidates will be monitored during their first 3 weeks after admission (Fig. 1). Motor functions will be assessed by a skilled neurologist, who will evaluate the need for gait rehabilitation. If and when the candidate is able to walk during a 2-min test, a final decision for inclusion will be made. Those candidates who do not exhibit sufficient walking capacities after 3 weeks will be excluded.

**Table 2 Tab2:** Inclusion and exclusion criteria

Inclusion criteria	Exclusion criteria
Patient with stroke, traumatic brain injury, or spinal cord injury in acute to subacute phase	Age <18 years
First stage of rehabilitation (<40 days after incident)	Clinically significant concomitant disease states (e.g., cardiovascular disease) that may threaten the patient’s health in case of sustained exercise
Need for gait rehabilitation because of at least one of the following conditions: • Paresis of the lower extremities • Severe balance disorders • No walking at admission	Concomitant gait disorders induced by acute to subacute musculoskeletal injuries (e.g., fracture of the lower extremities)
Ability to walk for 2 min without aid or with minimal aid, namely: • With the help of one person, or: • With walking aid (cane, walker)	Severe preexistent gait disorders that deeply affect walking abilities and gait pattern, either because of musculoskeletal (e.g., severe osteoarthritis) or neurological (e.g., Parkinson’s disease) etiologies
Informed consent as documented by signature	Severe noncorrected visual impairment.
	Inability to follow the procedures of the study, e.g., because of language problems, psychological disorders, dementia, etc.

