### Statistical analysis

Statistical analyses will be supervised by a skilled statistician and performed with MATLAB and STATA. We will analyze all randomized participants for whom the T1 assessment of the primary outcome and at least one training session are available (i.e., the “intention-to-treat” principle). The interim analysis, including 30 participants, will guide the final statistical methodology. The short-term efficacy of the intervention will be analyzed using the changes between T1 and T0. As the null hypothesis, we postulate that the change before and after the intervention (T1–T0) will not differ between the two groups. We will use simple comparison tests (*t* tests) and multiple regressions; in this case, intervention intensity (number of training sessions), disease etiology, and age will be used as covariates. Furthermore, we will longitudinally analyze (linear growth model) the gait parameters recorded in each gait training session; we hypothesize (H0) that the change over time will be equivalent between groups. We will also assess the difference between groups for the outcomes that are measured at T2 (3-month follow-up). Finally, as a subgroup analysis, we plan to analyze stroke survivors, TBI, and SCI patients separately.

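### The covariate list for the walking-speed change leaves out days from incident to T0, a baseline value already known, at some cost in precision but not in validity

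*Protocol article*

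**What the plan says.** All references are to the protocol article.

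- **Outcome.** Statistical analysis: "The short-term efficacy of the intervention will be analyzed using the changes between T1 and T0". Table 1 places T0 at week 0 and T1 at week 5.
- **Methods.** Same section: "We will use simple comparison tests (*t* tests) and multiple regressions". For the regressions, "intervention intensity (number of training sessions), disease etiology, and age will be used as covariates". Neither method is named as primary.
- **Status.** Same section: "The interim analysis, including 30 participants, will guide the final statistical methodology".
- **Design.** Assignment of interventions and blinding: 2:1 allocation, stratified by injury type (stroke, TBI, SCI) and nothing else. Allocation follows the T0 assessments.
- **Entry window.** Participants, Table 2: "First stage of rehabilitation (<40 days after incident". The text of the same section adds: "Potential candidates will be monitored during their first 3 weeks after admission".
- **Recovery over time.** Background: "In stroke patients, the maximum degree of recovery typically occurs within the first 3 months, then it progresses at a slower rate until 6 months".
- **Timing as a source of variation.** Sample size: differing measurement times across published stroke studies are one of the reasons given for having no preliminary power analysis.

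**The concern.** The outcome is a change over about five weeks of subacute recovery, so it contains spontaneous gain as well as any training effect. If that gain depends on how long after the incident T0 falls, days from incident to T0 explains part of the outcome variance. Etiology and age do not stand in for it. T0 walking speed, which is not listed either, would do so only in part, because two patients with the same T0 speed at different times since injury may have different gains ahead of them.

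The trial must know this value to apply its own entry criterion, yet neither the stratification nor the covariate list uses it. Recruitment is capped by an expected 35–50 eligible patients a year, so precision that needs no further patients is worth having. A chance imbalance in time since injury would also go unadjusted.

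**Working it through.** **1. The plan's own figure.** The sample size comes from expected recruitment, not from power. Per year: 20+10+5 = 35 to 25+15+10 = 50. Over two years: 70 to 100. This reproduces the stated range. The article gives no variance, effect size or power, so everything below in SD units rests on assumptions: two-sided alpha 0.05, 2:1 allocation, and an assumed partial R² for days from incident to T0 beyond the covariates already in the model.

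**2. How wide is the window?**
- If the 40-day limit applies at inclusion, T0 falls by about day 40.
- If it applies at admission, three weeks of monitoring can follow: 40 + 21 = 61 days.
- Taking T1 as about 35 days after T0, T1 falls by day 40 + 35 = 75 or day 61 + 35 = 96. Three months is about 91 days, so nearly all follow-up lies inside the fast phase that the Background describes.

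**3. Gain in precision.** Adjustment multiplies the residual variance by (1 − R²). The standard error is therefore multiplied by √(1 − R²), and the equivalent unadjusted sample size is N/(1 − R²). The last column gives the adjusted power for an effect that has 80% power unadjusted.

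| Assumed R² | SE ratio | Equivalent N (70) | Equivalent N (100) | Power |
|---|---|---|---|---|
| 0.02 | 0.990 | 71 | 102 | 81% |
| 0.05 | 0.975 | 74 | 105 | 82% |
| 0.10 | 0.949 | 78 | 111 | 84% |
| 0.15 | 0.922 | 82 | 118 | 86% |
| 0.20 | 0.894 | 88 | 125 | 88% |
| 0.30 | 0.837 | 100 | 143 | 92% |

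For R² of 0.05 to 0.15 the extra patients are 70/0.95 − 70 = 3.7 to 70/0.85 − 70 = 12.4, and 100/0.95 − 100 = 5.3 to 100/0.85 − 100 = 17.6.

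**4. Power at a fixed effect.** Assume 0.5 SD, noncentral t, arms of 47/23 and 67/33, and d = 0.5/√(1 − R²).
- N=70: 49% unadjusted, 51% at R² 0.05, 56% at R² 0.15.
- N=100: 64%, 67% and 71%.

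**5. Chance imbalance.** The SD of the arm difference in any baseline covariate, in covariate SDs, is √(1/n_c + 1/(2n_c)) with n_c = N/3. This is 0.254 at N=70 and 0.212 at N=100. A one-SD imbalance moves the estimate without the covariate by √R² times this. At R² 0.10 that is 0.316 × 0.254 = 0.08 outcome SD (N=70) and 0.316 × 0.212 = 0.07 (N=100). The differences detectable at 80% power are (1.96 + 0.84) times the same root, which gives 0.71 and 0.59 SD.

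**6. Validity.** A simulation under no treatment effect used 4,000 runs per setting, N=70 and 100, and R² of 0.05, 0.10 and 0.20. Without the covariate the mean estimate stayed within 0.005 SD of zero and type I error was 0.048–0.060. With it, type I error was 0.045–0.056. At N=100 and R² 0.20 the empirical standard error fell from 0.214 to 0.191, a ratio of 0.895, which matches the formula.

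**7. What R² might be.** The documents cannot say. An illustrative exponential recovery curve, with assumed time constants of 30–60 days and assumed between-patient variation, gives R² of 0.07–0.22 for T0 on days 7–40 and 0.16–0.38 for days 7–61. These values show only that the answer depends on the window and the curve.

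**The case against.** **A legitimate choice, and a provisional one.** Adjusting for the stratification factor and age is defensible, nothing in the article promises more, and the interim analysis is to guide the final methods. This is fair, and it is why the point is an improvement and not an error. But the article does name its covariates, and naming this one before any outcome data are examined avoids a later suspicion of selection.

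**The Background does not show a gradient within the window.** It speaks of stroke only and places the slowing after three months, while nearly all follow-up here ends before that. TBI and SCI make up 15–25 of the 35–50 eligible patients a year. This stands: an effect of timing inside the enrolled window is plausible, not documented. The Sample size section lends it some support by treating measurement time as a source of heterogeneity.

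**Two stronger readings.** A reader might infer that chance imbalance in time since injury biases the result. It does not: allocation is random, the estimate is unbiased over randomization, and its standard error already allows for such imbalance. A reader might also infer that a designated primary regression is at fault, or that T0 certainly extends to two months. The article lists t tests and regressions side by side without ranking them, and day 61 is reached only if the 40-day limit is counted at admission.

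**Weightier matters in the same sentence.** Number of training sessions is a post-randomization covariate, and T0 walking speed is missing. Both observations are right. The first is a separate point; the second is taken into the fix.

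**Conclusion.** The point holds as a low-cost gain in efficiency. The stated covariate list omits a baseline value that the trial already has and that plausibly predicts the change in walking speed. The treatment comparison remains valid without it.

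The size cannot be derived from the documents. Under an assumed partial R² of 0.02–0.30 the standard error would be about 1–16% smaller; near the bottom of that range the gain is negligible. The R² that matters is what days from incident to T0 adds beyond etiology, age and, once included, T0 walking speed. The increment over a model containing T0 speed was not calculated and may be smaller than the figures above.

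**What to change.** In Statistical analysis, before the 30-participant interim analysis, state that the regression of the T1–T0 change in walking speed will include as baseline covariates days from incident to T0 (continuous), T0 walking speed, etiology and age.

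The cost is one or two sentences of text and two model degrees of freedom. No new data are needed: the incident date is required for eligibility, and T0 speed is measured before allocation. With treatment, three etiologies and age in the model, 70 patients leave 70 − 5 = 65 residual degrees of freedom, and the two additions leave 63.

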### Trial objectives

The main goal of the GASPAR (Gait Adaptation for Stroke Patients with Augmented Reality) trial is to assess the efficacy of a treadmill training program that uses visually-guided stepping (AR) during the first phase of rehabilitation for patients with neurological gait disorders following a stroke. In addition, by the use of a pragmatic design, we seek to increase the generalizability and applicability of the study’s potential findings [28]. Consequently, in order to reflect the typical population in a neurorehabilitation center, we include patients with gait disorders of different etiologies; i.e., in addition to stroke patients, the study includes SCI and TBI patients who need gait rehabilitation. The AR program aims at three therapeutic goals: (1) to improve walking speed, which is important to ensure the independence of the patients in their daily lives, (2) to correct gait asymmetry, which may lead to their recovery of a more functional and physiological gait, thus improving gait coordination and reducing their risk of falls, and (3) to exercise gait agility, which may enhance patients’ adaptability to environmental changes while walking and hence again reduce fall risks. We also focus on assessment of the efficiency of the AR intervention. Specifically, we seek to document the patients’ adherence to, and compliance with, the program and to assess their tolerance for AR walking.

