### Assignment of interventions and blinding

Assignment is effected by a block randomization procedure with varying block size, implemented by independent researchers not affiliated with the GASPAR study. The STATA package RALLOC [30] is used to generate the sequences. The ratio between the intervention and the control group is 2:1; this facilitates recruitment [31] and provides a broader range of information and experience about the AR program. In addition, stratification is made according to the type of injury: stroke patients, TBI patients, and SCI patients. This procedure ensures the comparator and treatment groups to be populated by patients with comparable disease etiologies and thus facilitates interpretation of the results. Sequentially numbered, opaque, sealed envelopes are used to conceal the allocation. Informed consent is obtained by the principal investigator or his/her delegate. Inclusion is confirmed by the referring neurologist. After baseline assessments are taken (T0), the sealed envelope is opened to allocate the participant.

Given the nature of the intervention and its clinical setting, masking is not possible. However, the use of an objective measure as the primary outcome minimizes the risk of bias.

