### Sample size

An interim analysis based on 30 participants with complete data will be conducted to perform a power analysis and to compute the final sample size. The current estimation (as of June 2016) is that a total of 70 to 100 participants will be recruited. The reasons for such an approach are as follows: the hospitalization statistics for the years 2014 and 2015 show that about 300 patients per year were admitted for neurorehabilitation at the CRR, of which 70 were acute to subacute patients. Retrospective analyses of medical files over recent years indicate that 35–50 patients per year would have been eligible for the study: 20–25 stroke patients, 10–15 TBI patients, and 5–10 SCI patients. As a result, approximately 70–100 eligible candidates are expected over the 2-year framework of the study. The uncertainty of this number results from the substantial year-to-year variability seen in patients’ profiles. A preliminary power analysis is not possible for two reasons: (1) the data currently available in the literature about walking speed in acute to subacute TBI and SCI patients are sparse and inconsistent, and (2) while more studies report changes in walking speeds in stroke patients [35], a substantial heterogeneity exists concerning the time of measurement and inclusion criteria for these studies. As a result, we do not have yet sufficient information to estimate the variance of our principal outcome. Consequently, we plan to assess the variance of the outcomes and the effect sizes with an interim analysis based on 30 subjects. The definitive sample size will be assessed accordingly.

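### Analysing stroke, TBI and SCI patients separately does not test whether the effect differs by etiology, and with strata this small it can easily give mixed results when the effect is the same in all three

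*Protocol article*

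**What the plan says.** The subgroup method is the last item under Statistical analysis in the protocol article: "Finally, as a subgroup analysis, we plan to analyze stroke survivors, TBI, and SCI patients separately". For the T1–T0 change, the same paragraph names t tests and multiple regressions, and in the regressions "intervention intensity (number of training sessions), disease etiology, and age will be used as covariates". No arm-by-etiology term is mentioned.

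The expected case mix is under Sample size: "35–50 patients per year would have been eligible for the study", made up of "20–25 stroke patients, 10–15 TBI patients, and 5–10 SCI patients", so that "approximately 70–100 eligible candidates are expected over the 2-year framework of the study". Under Assignment of interventions and blinding, "The ratio between the intervention and the control group is 2:1", with randomization stratified by type of injury. The article gives no effect size, standard deviation, alpha or power. It leaves the final sample size to an interim analysis of 30 participants.

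**The concern.** A covariate for etiology adjusts for differences in average recovery between etiologies. It does not ask whether the benefit of augmented reality differs between them. Three within-stratum results do not ask that either: significance in one stratum and not in another is not a test of the difference between them.

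The strata also differ greatly in size. If the benefit were identical in all three, the chance of reaching significance would still fall from stroke to TBI to SCI. A finding that the program works in stroke but not in SCI could therefore reflect nothing but the number of patients. The stake is a false claim of etiology-specific benefit, or of its absence.

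**Working it through.** **Inputs from the article.** Yearly eligible patients: stroke 20–25, TBI 10–15, SCI 5–10. Duration: 2 years. Allocation: 2:1 within etiology strata.

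**Assumptions, because the article gives no figures.** Two-sided alpha 0.05, effects in SD units from 0.3 to 1.0, no dropout (the case most favourable to the plan), an unadjusted t test in each stratum.

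**Step 1, the article's own total.** 2 × (20+10+5) = 70 and 2 × (25+15+10) = 100. The stated 70–100 is reproduced.

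**Step 2, stratum sizes (comparator/AR) and detectable effects.** Power comes from the noncentral t distribution with n − 2 degrees of freedom and noncentrality d / √(1/n_C + 1/n_A). The 95% CI half-width is t(0.975, n − 2) × √(1/n_C + 1/n_A).

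| Total | Stratum | n_C / n_A | Effect detectable with 80% power | CI half-width |
|---|---|---|---|---|
| 70 | Stroke | 13 / 27 | 0.97 SD | 0.68 SD |
| 70 | TBI | 7 / 13 | 1.39 SD | 0.98 SD |
| 70 | SCI | 3 / 7 | 2.21 SD | 1.59 SD |
| 100 | Stroke | 17 / 33 | 0.85 SD | 0.60 SD |
| 100 | TBI | 10 / 20 | 1.12 SD | 0.79 SD |
| 100 | SCI | 7 / 13 | 1.39 SD | 0.98 SD |

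The pooled comparison detects 0.72 SD (N=70) or 0.60 SD (N=100).

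**Step 3, mixed results under one common effect.** Let p_k be the chance that stratum k is significant in favour of AR. The strata are independent, so P(mixed) = 1 − Πp_k − Π(1 − p_k). At 0.6 SD and N=70, p = 0.410, 0.227 and 0.117, so P(mixed) = 1 − 0.011 − 0.403 = 0.59. At N=100, p = 0.504, 0.321 and 0.227, so P(mixed) = 1 − 0.037 − 0.260 = 0.70.

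| Common effect | Mixed, N=70 | Mixed, N=100 |
|---|---|---|
| 0.3 SD | 26% | 32% |
| 0.5 SD | 47% | 59% |
| 0.6 SD | 59% | 70% |
| 0.8 SD | 77% | 78% |
| 1.0 SD | 83% | 65% |

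Counting significance in either direction changes only the small-effect end noticeably (27% and 33% at 0.3 SD). All three strata are significant at 0.6 SD in only about 1% (N=70) or 4% (N=100) of trials.

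**Step 4, no effect anywhere.** P(at least one stratum significant) = 1 − 0.95³ = 0.143 in either direction. In favour of AR alone it is 1 − 0.975³ = 0.073.

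**Step 5, power of the interaction test.** This is an F test with 2 and N − 6 degrees of freedom and noncentrality Σw_k(δ_k − δ̄)², where w_k = 1/(1/n_C + 1/n_A) and δ̄ is the weighted mean effect. At N=70 the weights are 8.78, 4.55 and 2.10.

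| True effect, stroke / TBI / SCI | Power, N=70 | Power, N=100 |
|---|---|---|
| 0.8 / 0.8 / 0 SD | 14% | 25% |
| 0.8 / 0.4 / 0 SD | 15% | 24% |
| 0.8 / 0 / 0 SD | 26% | 37% |

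**The case against.** The case against has several parts.

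- **The article does not say that significance will be declared in each stratum.** It speaks of analysing, labels this a subgroup analysis and places it last. This is fair. Reading it as three tests is an inference, though a natural one, because t tests are named in the same paragraph.
- **A condensed article may leave the interaction term, interval reporting and exploratory label to an analysis plan, and the interim analysis is to guide the final methodology.** Their absence alone would not be a finding. But the article does state a method, separate analysis, and that method does not answer the question.
- **The interaction test is weak, and with a full interaction and no other covariates the stratum point estimates equal those from separate analyses.** Both are true. The gain is one test of the right question and a pooled residual variance.

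Two stronger readings are tempting and are not supported. A reader might infer that the three analyses will necessarily contradict each other. At 0.3 SD the commonest outcome is no significant stratum (about 74% at N=70, 68% at N=100). Mixed results would be almost entirely significant versus non-significant: even at 0.3 SD, the chance that a stratum significantly favours the comparator is below 1%.

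A reader might also infer, because Trial objectives words the main goal "for patients with neurological gait disorders following a stroke", that the stroke subgroup carries the trial's real question. The same paragraph goes on to explain why SCI and TBI patients are included, and the Abstract and Trial design state the objective without reference to stroke. The wording is loose, but the pooled population is plainly intended.

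**Conclusion.** The concern holds in this form: the stated subgroup method cannot show whether the effect differs by etiology, and no other analysis in the article does so. If its results are read as three tests, mixed results under an identical effect are a substantial risk at every size considered. They are more likely than not from 0.6 SD upward at N=70 and from 0.5 SD upward at N=100.

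The percentages rest on the assumed alpha, effect range and absence of dropout, and on the article's expected case mix. The final sample size may change after the interim analysis. Dropout would make the strata smaller. The argument that separate results do not test a difference needs none of these assumptions. The main pooled comparison is not affected.

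**What to change.** Replace the sentence on separate analyses. Fit the all-participant regression of the T1–T0 change with an added arm-by-etiology interaction. Report the interaction test and the three etiology-specific treatment effects with 95% confidence intervals from that model, labelled exploratory, and make no significance claims within subgroups.

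State two limits beside it. First, the test's power is low, so a non-significant interaction is not evidence of equal effects. Second, the pooled model assumes similar residual variance across etiologies. If that assumption is acceptable, it narrows the smallest stratum's interval somewhat: for SCI at N=70 the half-width goes from 2.306 × 0.690 = 1.59 SD to about 1.998 × 0.690 = 1.38 SD.

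The cost is a change of analysis wording. Recruitment, randomization and data collection stay as they are.
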